### 2.4 Exclusion criteria

Any participants will be excluded when they have one of the following conditions: 1) multiple primary tumors; 2) prior usage of immunomodulator drugs or any medicines having a direct impact on the immune system; 3) pregnancy or lactation for women; 4) history of allergy to the tested medications or light sensitiveness; 5) contraindication to gastroscopy; 6) comorbidities including autoimmune disease, severe cardiovascular disease, mental illness or severe neurosis, gastrointestinal bleeding and other severe diseases; 7) other inappropriate condition for inclusion determined by the researchers.

### 2.5 Study interventions

Included patients will be divided into the test group and control group. In the test group, patients will receive a PDT operation followed by ICI plus chemotherapy. In the control group, only ICI plus chemotherapy will be performed. 48 h before the PDT procedure, a photosensitizer (hematoporphyrin injection, Hiporfin^®^) will be intravenously injected into the patients in the test group. The dose of photosensitizer is determined based on the weight of patients after carefully evaluating the patient’s kidney and liver function (3–5 mg/kg). Patients with injected photosensitizer will be kept in the dark ward to avoid light exposure until the PDT operation. During the PDT operation, basal anesthesia will be given to the patient first. Then, a gastroscope-based PDT treatment will be administered with a 630 nm laser light delivered by a cylindrical fiber. The cylindrical fiber will be placed near the tumor to ensure complete illumination, and a multi-fractions illumination may be used in some cases (e.g., the tumor is too large to illuminate within one fraction of illumination). The laser light will be generated by the semiconductor laser photodynamic therapy instrument (PDT 630II, Guilin Xingda Photoelectric Medical Equipment Co., Ltd). The parameter of illumination will be set as 800 mW for 15 min with a total energy of 720J. Considering the advanced patients we will include, the patients will receive PDT illumination for four continuous days with the same procedure. After the PDT treatment, patients will be avoided direct light exposure for at least 1 month. In the second week after PDT, patients will receive ICI (Sintilimab or Camrelizumab, 200 mg, day 1, every 3 weeks) plus chemotherapy [SOX (Tegafur gimeracil oteracil potassium capsule twice a day, day 1–14, and oxaliplatin 130 mg/m^2^, day 1, every 3 weeks) or XELOX (capecitabine 1,000 mg/m^2^ twice a day, days 1–14, and oxaliplatin 130 mg/m^2^, day 1, every 3 weeks)]. Tegafur gimeracil oteracil potassium capsule and capecitabine will be orally administered, and others will be intravenously administered. PDT will be only used in the first cycle of treatment for the patients in the test group, which means only ICI plus chemotherapy will continue in the following cycles of treatment. For patients in the control group, the same ICI plus chemotherapy scheme will be given, but no prior PDT operation will be performed in the first treatment cycle.

### 2.6 Termination of the trial

All regimens will continue until confirmed disease progression, unacceptable toxicity, drop out, or the study end. The study end for a subject is defined as treatment up to eight cycles. After eight cycles, patients will continue the treatment or change a new scheme according to the judgment of the investigator.

### 2.7 Outcomes

The primary outcomes are objective response rate (ORR) and progression-free survival (PFS). The best overall response from ICI plus chemotherapy initiation to disease progression or last follow-up will be used to analyze the ORR. ORR refers to the proportion of patients with complete response (CR) and partial response (PR). PFS is defined as the time from ICI plus chemotherapy initiation to the date of first documented tumor progression or death no matter which happens first. All evaluations of treatment response or progression will be conducted by experienced radiologists according to the RECIST 1.1 criteria (Eisenhauer et al., 1990). The safety will be assessed using the incidence of adverse events defined as any toxicity from intervention initiation to the study end according to the NCI-CTCAE 5.0 criteria (Institute, 2017). For patients who receive PDT treatment, a self-control assessment before and after PDT will be performed, in which the changes in peripheral blood mononuclear cells (PBMCs) and intratumoral gene expression profiles will be evaluated.

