### 2.8 Investigation methods

The tumor will be assessed using contrast-enhanced CT of the abdomen at baseline and each following visit for all included patients. According to the NCI-CTCAE 5.0, any adverse event during the study will be recorded with their types, severity, start and end time, and relatedness to interventions. Blood and tumor tissue specimens before and after PDT will be collected from PDT-treated patients for corresponding tests. After the pre-processing of the blood specimens, PBMC analysis will be performed using flow cytometry to detect the following cells: total T lymphocytes (CD3^+^), cytotoxicity T cells (CD8^+^), CD4^+^ T cells (CD4^+^), and T regulatory cells (Tregs, CD4^+^ CD25^+^ FOXP3^+^). Specimens of tumor tissues will be assessed with an RNA-seq test to investigate the spatiotemporal changes in the expression profile. All patients will receive tumor histological examination [HE stain and immunohistochemistry (IHC)], routine laboratory studies, ECG, chest X scan, ECOG scoring, physical examination, and records of vital signs and concomitant medications. The work timeline and corresponding investigated items are listed in Table 1.

**TABLE 1 T1:** Schedule for the important events in this trial.

Items	Screening phase (within 1 week)	Treatment phase				Follow up phase
		Test group			Control group	
		Cycle 1 (before PDT)	Cycle 1 (after PDT and before ICI plus chemotherapy)	Cycle 1 and beyond (day 1 for ICI plus chemotherapy)	Cycle 1 and beyond (day 1 for ICI plus chemotherapy)	
Informed consent	X					
Inclusion and exclusion criteria	X					
Tumor histological examination	X					
Medical history	X					
Physical examination	X			X	X	X
Vital signs	X			X	X	X
Performance status (ECOG)	X			X	X	X
Concomitant medications	X			X	X	X
Electrocardiogram (ECG)	X					
Chest X scan	X					
Laboratory tests (including blood routine examination, chemistry test, coagulation function, tumor marker, and thyroid function)	X			X	X	X
Pregnancy test (women only)	X			X	X	X
Photosensitizer injection and skin test		X				
Collection and analysis of blood and tumor tissue specimens		X	X			
Tumor assessment by CT	X		X	X (in the cycle 2, 4, 6, and 8)	X (in the cycle 2, 4, 6, and 8)	X
Adverse events assessment		Continuously				X

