### 2.9 Follow up

Assessment of treatment response will be performed every two cycles for a maximum of eight cycles. The first tumor assessment will be done within 1 weeks before ICI plus chemotherapy initiation and after PDT if PDT is administered in this subject. Reports of adverse events will be obtained during the whole study period through patient interviews or phone contacts. For PDT-treated patients, blood and tumor specimens will be obtained before light illumination on the day of the PDT operation and 48 h after the PDT operation. Diseases examinations and laboratory studies will be repeated at each cycle of treatment and 1 month after the last dose is received.

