### 2.14 Data monitoring

The trial process will be monitored by the institutional data safety monitoring committee at regular intervals (at least annually). All event reports of toxicities, treatment discontinuation, and transformation will be recorded and submitted to the data monitoring committee. The primary investigator will decide to continue or abort the trial based on the safety assessment from the data safety monitoring and ethics committee.

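### The best-response window for ORR has no cut-off at the start of other anticancer treatment, and the protocol's sections disagree on when response assessment ends

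*Protocol article*

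**What the plan says.** Section 2.7 names ORR as a primary outcome together with PFS (the abstract lists it as secondary), and section 2.11 bases the sample size on it. The window is stated outright in section 2.7: "The best overall response from ICI plus chemotherapy initiation to disease progression or last follow-up will be used to analyze the ORR". Last follow-up is not defined anywhere.

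Four other statements bear on when that window closes:

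- Section 2.6, on when treatment stops: "All regimens will continue until confirmed disease progression, unacceptable toxicity, drop out, or the study end". Toxicity and the study end are both ways to stop without progression.
- Section 2.6, on the end of study for one patient: "The study end for a subject is defined as treatment up to eight cycles". It continues: "After eight cycles, patients will continue the treatment or change a new scheme according to the judgment of the investigator".
- Section 2.9: "Assessment of treatment response will be performed every two cycles for a maximum of eight cycles". The same section repeats examinations 1 month after the last dose.
- Section 2.8, Table 1: the row "Tumor assessment by CT" is marked in cycles 2, 4, 6 and 8 and again in the follow-up phase, for which the table gives no timing.

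**The concern.** ORR is meant to describe response to the assigned regimen. The window can stay open after a patient has left that regimen without progressing, and nothing closes it when other anticancer treatment begins. If such a patient first reaches CR or PR at a later scan, the rule in section 2.7 credits that response to the randomised arm.

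With 30 patients per arm, single patients are visible in the result. The trial is also open-label, so decisions to stop or switch need not be equally frequent in the two arms. Separately, two analysts following the text could close the window at different scans: one at cycle 8 under section 2.9, the other at the follow-up CT under section 2.7 and Table 1.

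**Working it through.** **1. The plan's own figure.** Inputs from section 2.11: ORR 50% against 85%, two-sided 5%, power 80%, 20% dropout, 30 per arm. With the unpooled normal approximation:

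n = (1.960 + 0.842)² × (0.50×0.50 + 0.85×0.15) / 0.35² = 24.19 per arm.

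Then 24.19 / 0.8 = 30.2, or 25 × 1.2 = 30, per arm. The stated 60 reproduces. This point contests no figure and leaves the sample size as it is.

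**2. When does the window close?** The places side by side:

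| Place | What it implies |
|---|---|
| 2.7 | Open until progression or last follow-up |
| 2.6 | The patient's study end is at most eight cycles; a new scheme may follow |
| 2.9 | Response assessed up to eight cycles; examinations 1 month after the last dose |
| Table 1 | CT at cycles 2, 4, 6 and 8, and again in follow-up |

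Under section 2.9 alone, the follow-up CT is not a response assessment. Under section 2.7 it is, because it falls before or at last follow-up.

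**3. Who is exposed?** Only patients who have not responded, have not progressed and have left the assigned regimen. Progression already closes the window, so progressed patients do not belong in the count. Two routes remain:

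- *After eight cycles.* A new scheme is expressly allowed, and the follow-up CT can come after it starts. The only timing given for post-treatment examinations is 1 month after the last dose, so this interval is short.
- *Early stop without progression.* Eight 3-week cycles are 24 weeks. A patient stopping after two cycles (6 weeks) has 24 − 6 = 18 weeks left before the cap. The text does not say whether the scans continue, but PFS is also primary and runs to progression or death, so continued scanning would be expected. Other treatment in this interval is neither permitted nor barred.

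**4. Size per patient.** One misattributed response moves an arm's ORR by 1/30 = 3.3 points. Starting from the planned 35-point difference:

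- none: 35 points
- one in the control arm: 35 − 3.3 = 31.7 points (control ORR 15/30 = 50% becomes 16/30 = 53.3%)
- one in the test arm: 35 + 3.3 = 38.3 points
- one in each arm: 35 points

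**5. Illustration on power.** Let f be an assumed share of the 15 expected control non-responders who are later counted as responders. Control ORR becomes 0.50 + 0.50f. Pooled normal approximation, 30 per arm, no dropout:

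| f (patients) | Control arm only | Same f in both arms |
|---|---|---|
| 0 (0) | 84.3% | 84.3% |
| 5% (0.75) | 79.0% | 81.2% |
| 10% (1.5) | 72.9% | 77.9% |

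The documents give no value for f, and zero is possible. Since some of the 15 will have progressed, a given f needs a higher conversion rate among those still at risk.

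**The case against.** The strongest reply is that the exposure is narrow. Section 2.9 caps response assessment at eight cycles, and section 2.6 allows a new scheme only after that point. What is left is roughly one CT, plus early stoppers whose later treatment and scanning the text does not describe. This stands, and it is why the point is small. It does not remove the conflict with section 2.7 and Table 1.

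A second reply is that handling of later therapy belongs in the full protocol or SAP, or that counting all responses is a coherent treatment-policy reading under intention to treat. An omission could be left to those documents, but section 2.7 states the window and names its closing events. An SAP that closed it earlier would contradict the protocol. No passage says that responses after a switch are meant to count. The per-protocol analysis in section 2.13 need not help, because a switch after eight cycles is allowed and so is not a deviation.

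A reader might go further and infer that controls could receive PDT and be scored as responders to ICI plus chemotherapy alone. The documents do not support that as a finding. Section 2.5 gives controls ICI plus chemotherapy only and confines PDT to the first cycle of the test group, and no crossover is described. Nor does section 2.6 extend its new-scheme permission to patients who stop early for toxicity.

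**Conclusion.** The point holds in limited form. Section 2.7 lets a response first seen after a switch count for the randomised arm, and sections 2.6, 2.7, 2.9 and Table 1 do not agree on when response assessment ends. The size is 3.3 points of an arm's ORR per affected patient, from zero upward. A reader might infer that the planned contrast will shrink by a known amount. It will not bear that reading: no switching rate is given, and the bias may go either way or cancel. The power figures rest on assumed values of f and show only that one or two patients matter at this sample size. This is a cheap improvement to an endpoint definition and does not undermine the design.

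**What to change.** In section 2.7, close the best-response window at the earliest of:

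- progression;
- the last scheduled response assessment, naming the scan;
- the start of any anticancer treatment outside the assigned regimen.

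Count a patient without a response by then as a non-responder. Record the date of the first non-assigned anticancer treatment. Reconcile sections 2.6, 2.7, 2.9 and Table 1 on when response assessment ends, including whether the follow-up CT counts, and define last follow-up.

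The cost is about one sentence in section 2.7, matching wording elsewhere and one date field. Much of the information is already collected: Table 1 records concomitant medications at each cycle and in follow-up, and section 2.14 says "All event reports of toxicities, treatment discontinuation, and transformation will be recorded". The sample size and patient management do not change. The downside is that ORR may be slightly lower, because late responses on other treatment no longer count.

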### 2.8 Investigation methods

The tumor will be assessed using contrast-enhanced CT of the abdomen at baseline and each following visit for all included patients. According to the NCI-CTCAE 5.0, any adverse event during the study will be recorded with their types, severity, start and end time, and relatedness to interventions. Blood and tumor tissue specimens before and after PDT will be collected from PDT-treated patients for corresponding tests. After the pre-processing of the blood specimens, PBMC analysis will be performed using flow cytometry to detect the following cells: total T lymphocytes (CD3^+^), cytotoxicity T cells (CD8^+^), CD4^+^ T cells (CD4^+^), and T regulatory cells (Tregs, CD4^+^ CD25^+^ FOXP3^+^). Specimens of tumor tissues will be assessed with an RNA-seq test to investigate the spatiotemporal changes in the expression profile. All patients will receive tumor histological examination [HE stain and immunohistochemistry (IHC)], routine laboratory studies, ECG, chest X scan, ECOG scoring, physical examination, and records of vital signs and concomitant medications. The work timeline and corresponding investigated items are listed in Table 1.

**TABLE 1 T1:** Schedule for the important events in this trial.

Items	Screening phase (within 1 week)	Treatment phase				Follow up phase
		Test group			Control group	
		Cycle 1 (before PDT)	Cycle 1 (after PDT and before ICI plus chemotherapy)	Cycle 1 and beyond (day 1 for ICI plus chemotherapy)	Cycle 1 and beyond (day 1 for ICI plus chemotherapy)	
Informed consent	X					
Inclusion and exclusion criteria	X					
Tumor histological examination	X					
Medical history	X					
Physical examination	X			X	X	X
Vital signs	X			X	X	X
Performance status (ECOG)	X			X	X	X
Concomitant medications	X			X	X	X
Electrocardiogram (ECG)	X					
Chest X scan	X					
Laboratory tests (including blood routine examination, chemistry test, coagulation function, tumor marker, and thyroid function)	X			X	X	X
Pregnancy test (women only)	X			X	X	X
Photosensitizer injection and skin test		X				
Collection and analysis of blood and tumor tissue specimens		X	X			
Tumor assessment by CT	X		X	X (in the cycle 2, 4, 6, and 8)	X (in the cycle 2, 4, 6, and 8)	X
Adverse events assessment		Continuously				X

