### 2.3 Inclusion criteria

All patients who meet the following criteria will be enrolled: 1) 18–65 years old; 2) untreated gastric or gastroesophageal junction adenocarcinoma confirmed by histopathological examination; 3) advanced or metastatic stage; 4) ECOG score 0–2; 5) expected survival >6 months; 6) having at least one measurable lesion; 7) adequate bone marrow, kidney and liver function defined as neutrophil count ≥1.5 × 10^9^/L, platelet count ≥100 × 10^9^/L, creatinine ≤1.5 times the upper limit of normal (ULN), total bilirubin ≤1.5 times the ULN, and aspartate transaminase and alanine aminotransferase ≤5.0 times the ULN; 8) and providing signed informed consent.

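### Scheduled tumour imaging covers only the abdomen, although eligibility allows measurable disease at any site and ORR and PFS are to be judged by RECIST 1.1

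*Protocol article*

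**What the plan says.** All references are to the protocol article.

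- **Imaging field (2.8):** "The tumor will be assessed using contrast-enhanced CT of the abdomen at baseline and each following visit for all included patients".
- **Chest (2.8 and Table 1):** the text lists "routine laboratory studies, ECG, chest X scan, ECOG scoring, physical examination" among the general examinations. Table 1 marks the chest scan in the screening column and nowhere else.
- **Pelvis:** no section names pelvic imaging.
- **Schedule (Table 1):** the row "Tumor assessment by CT" is marked at screening, after PDT in the test group, in cycles 2, 4, 6 and 8, and at follow-up. It names no body region.
- **Eligibility (2.3):** "untreated gastric or gastroesophageal junction adenocarcinoma confirmed by histopathological examination", at "advanced or metastatic stage", and "having at least one measurable lesion". The site of the measurable lesion is not restricted.
- **Endpoints (2.7):** ORR and PFS are both named as primary. "All evaluations of treatment response or progression will be conducted by experienced radiologists according to the RECIST 1.1 criteria". PFS ends at the first documented progression or death.
- **Follow-up (2.9):** disease examinations are repeated at each cycle and one month after the last dose. Which examinations these are is not said.

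**The concern.** Eligibility, imaging field and endpoint do not fit together. A patient with metastatic or junctional disease may have lesions in the chest or pelvis at entry, or develop them later, and the planned scans do not look there. Two separate problems follow.

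1. **PFS.** Progression must be documented to count. Disease that appears or grows outside the scanned field is not documented on schedule, so its event date may be late or absent.
2. **ORR.** A patient can satisfy the measurable-lesion criterion with a lesion that the assessment CT never covers. On the planned scans that patient has no target lesion to follow. Conversely, a patient whose abdominal lesions shrink may be called a responder while carrying an unseen new lesion elsewhere.

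Baseline scans cannot be obtained afterwards, so the gap has to be closed before patients are enrolled.

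**Working it through.** **Is the restriction stated, or only inferred?** It is stated. Section 2.8 names the abdomen and applies it to all patients. The CT row in Table 1 gives no region, so it neither widens nor contradicts that. The repeated examinations in 2.9 are unspecified, and Table 1 schedules no repeat chest imaging under any row.

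**What each gap does to each endpoint**

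| Situation | PFS | ORR |
|---|---|---|
| New or growing lesion only in chest or pelvis | event late or absent: PFS too long | a responder may carry an unseen new lesion: ORR too high |
| Only measurable lesion outside the abdomen | growth of that lesion not seen on schedule: PFS too long | response cannot be scored; if counted as non-response, intention-to-treat ORR too low |

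The PFS column points one way. The ORR column points both ways, and the document gives no frequencies with which to net them.

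**The plan's own sample size, for context.** Inputs from 2.11: ORR 50% versus 85%, two-sided 5%, power 80%, dropout 20%, 30 per arm. With unpooled variance,

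n = (1.960 + 0.842)² × (0.50×0.50 + 0.85×0.15) / 0.35² = 7.849 × 0.3775 / 0.1225 = 24.19 per arm.

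Rounding up to 25 and multiplying by 1.2 gives 30; 24.19/0.8 gives 30.2. The planned 60 is therefore reproduced. The present point does not depend on it.

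**Illustration for ORR.** Let u be the share of patients with no measurable lesion in the abdominal field. The document gives no value, so u is assumed. If these patients count as non-responders, the rates become p₁ = 0.50(1−u) and p₂ = 0.85(1−u). Power of the pooled two-proportion test with n per arm is

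Φ{ [ (p₂−p₁)√n − 1.960√(2p̄(1−p̄)) ] / √(p₁(1−p₁)+p₂(1−p₂)) }, with p̄ = (p₁+p₂)/2.

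For u = 0 and n = 30: (0.35×5.477 − 1.960×0.6624)/0.6144 = (1.917 − 1.298)/0.6144 = 1.007, so power is 84%.

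| u (assumed) | p₁ | p₂ | power, n = 30 | power, n = 24 |
|---|---|---|---|---|
| 0 | 0.500 | 0.850 | 84% | 75% |
| 5% | 0.475 | 0.8075 | 78% | 68% |
| 10% | 0.450 | 0.765 | 72% | 61% |
| 20% | 0.400 | 0.680 | 59% | 49% |

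The last column uses 30 × 0.8 = 24 per arm, the number left after the plan's 20% dropout. Each single unscorable patient is 1/30 = 3.3 percentage points of an arm's ORR.

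**PFS.** No calculation is possible. The document gives no control median, no hazard ratio and no distribution of progression sites.

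**The case against.** The strongest reply is that the gap is narrower than it looks, and much of that reply stands.

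- **Extra-abdominal progression is not excluded from PFS.** A reader might infer that it never counts. The definition in 2.7 has no abdominal limit, so any documented progression counts, as does death. Physical examination, ECOG status and tumour markers are repeated, and unscheduled imaging is possible. The supported wording is that scheduled imaging may miss it or find it late.
- **Most patients can probably be scored.** PDT is given through a gastroscope with the fibre near the tumour, which implies a tumour in place in the stomach or at the junction. Only patients whose sole measurable disease is outside the field are unscorable, and the document does not show how many there are, if any.
- **ORR is not shown to be overstated.** Unscorable patients push an intention-to-treat ORR down and unseen new lesions push it up.
- **A bias in favour of PDT is not shown.** It is tempting to argue that an abdominal field captures local shrinkage at the treated stomach and hides distant failure, so that a local effect passes for a systemic one. But the abdomen also contains distant sites such as liver and abdominal nodes, and the same field applies to both arms. Open-label unscheduled imaging could differ by arm. That too is a possibility, not a finding.
- **This is a condensed article.** A fuller imaging rule may exist elsewhere. That carries little weight here, because the article states the region outright instead of leaving it open.

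**Conclusion.** The point holds in limited form. Section 2.8 sets an imaging field narrower than the disease that section 2.3 admits and that section 2.7 claims to assess by RECIST 1.1. Late or missed detection of thoracic or pelvic progression would overstate PFS in both arms; the amount cannot be computed. For ORR the net direction is unknown.

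The power figures (84% falling to 78-59% for u of 5-20%, 30 per arm) rest on three assumptions: the value of u, counting unscorable patients as non-responders, and no dropout. They show sensitivity, not an expected loss. A reader might infer from them that the trial is underpowered for this reason, or from the abdominal field that the comparison favours PDT. The document supports neither. This is an inexpensive improvement that should be made, not a defect that invalidates the trial.

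**What to change.** 1. **Section 2.3:** require at least one measurable lesion within the CT field used for response assessment. This is a wording change and costs nothing in procedures. It would still be needed if the field stays abdominal, though alone it leaves extra-abdominal progression uncovered.
2. **Section 2.8 and Table 1:** extend the same CT session to chest, abdomen and pelvis at baseline and at every scheduled tumour assessment, identically in both arms, and name the region in the Table 1 row. The cost is somewhat more radiation dose and reading time; no extra visit is needed and the planned sample size does not change.
3. **If the field stays abdominal:** state that scheduled detection of progression is limited to the abdomen, and restrict the PFS and ORR conclusions accordingly.
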